## Abstract

**Background:**

One of the main goals of cardiopulmonary bypass (CPB) is targeting an adequate mean arterial pressure (MAP) during heart surgery, in order to maintain appropriate perfusion pressures in all end-organs. As inheritance of early studies, a value of 50–60 mmHg has been historically accepted as the “gold standard” MAP. However, in the last decades, the CPB management has remarkably changed, thanks to the evolution of technology and the availability of new biomaterials. Therefore, as highlighted by the latest European Guidelines, the current management of CPB can no longer refer to those pioneering studies. To date, only few single-centre studies have compared different strategies of MAP management during CPB, but with contradictory findings and without achieving a real consensus. Therefore, what should be the ideal strategy of MAP management during CPB is still on debate. This trial is the first multicentre, randomized, controlled study which compares three different strategies of MAP management during the CPB.

**Methods:**

We described herein the methodology of a multicentre, randomized, controlled trial comparing three different approaches to MAP management during CPB in patients undergoing elective cardiac surgery: the historically accepted “standard MAP” (50–60 mmHg), the “high MAP” (70–80 mmHg) and the “patient-tailored MAP” (comparable to the patient’s preoperative MAP). It is the aim of the study to find the most suitable management in order to obtain the most adequate perfusion of end-organs during cardiac surgery. For this purpose, the primary endpoint will be the peak of serum lactate (Lmax) released during CPB, as index of tissue hypoxia. The secondary outcomes will include all the intraoperative parameters of tissue oxygenation and major postoperative complications related to organ malperfusion.

**Discussion:**

This trial will assess the best strategy to target the MAP during CPB, thus further improving the outcomes of cardiac surgery.

**Trial registration:**

NCT05740397 (retrospectively registered; 22/02/2023)

## Administrative information

Note: the numbers in curly brackets in this protocol refer to SPIRIT checklist item numbers. The order of the items has been modified to group similar items (see http://www.equator-network.org/reporting-guidelines/spirit-2013-statement-defining-standard-protocol-items-for-clinical-trials/).

## Introduction

### Background and rationale {6a}

Most of cardiac surgery operations require a bloodless operating field and a steady heart (i.e. cardioplegic arrest). To ensure the perfusion of peripheral organs during the cardioplegic arrest time, the cardiopulmonary bypass (CPB) is installed. The CPB is a biomedical device, also named Heart-Lung machine, that, through a circuit, filtrates and oxygenates the venous blood of the patient, giving it back as arterial blood through a mechanical pump. The target blood flow during CPB is traditionally determined according to body surface area (BSA) and temperature. Under moderate hypothermia-to-normothermic conditions, the pump flow rate is set between 2.2 and 2.8 l/min/m^2^ by the majority of perfusionists [1]. Therefore, the CPB provides continuous blood flow, so the pressure produced is a “mean arterial pressure” (MAP). The MAP can be modulated by vasoactive and/or anaesthetic drugs, in order to maintain an appropriate perfusion pressures in all end-organs, particularly the kidneys, the brain and the gastrointestinal tract, avoiding tissue hypoperfusion and hypoxia. The latter, indeed, may occur in the postoperative period as organ damage: cerebral ischaemia and consequently transitory or permanent neurological injury [2], renal ischaemia and consequently acute kidney injury [3, 4], or gastrointestinal ischaemia [5, 6]. Therefore, the hypoperfusion during CPB could directly affect the morbidity and mortality of cardiac surgery. Consequently, the management of MAP acquires a crucial role. A value of 50–60 mmHg has been historically accepted as the “gold standard” MAP, according to the pioneering animal experiments and investigations of the dawn of cardiac surgery (around ‘50s) [2, 7–11]. However, in the last decades, the CPB has remarkably changed thanks to the evolution of technology and the availability of new biomaterials. Therefore, as highlighted by the latest European Guidelines [1], the current management of CPB can no longer refer to those pioneering studies. To date, only few authors focused their attention on the correlation between MAP values during CPB and cardiac surgery outcomes. Vedel et al. [12] compared the “high-target” MAP (70–80 mmHg) to “standard” MAP (50–60 mmHg) in terms of new postoperative cerebral injuries. They reported a higher incidence of stroke (7.0% vs 1.1%; *P*=0.09) and mortality (4.1% vs 0%; *P*=0.06) in the “high-target” MAP population compared to the “low-target” group. Conversely, Gold et al. [13] reported a reduction (from 12.9 to 4.8%) of major cardiac and neurologic events in patients treated with higher MAP compared to patients treated with the “standard” MAP during coronary artery bypass graft surgery (CABG). However, the abovementioned studies are both from a single institution, with small and selected sample sizes (i.e. CABG). Finally, Charleson et al. [14] compared the “high MAP” (80 mmHg) with “patient-tailored” MAP (comparable to pre-operative MAP of the single patient). The study showed no differences in terms of major cardiac and neurologic events (11.7 and 12.6% respectively). However, also this study included only patients undergoing CABG surgery. However, all the these investigations showed conflicting evidences, without achieving a real consensus on what should be the most adequate MAP target during CPB.

The purpose of our randomized study is to define the best strategy to obtain an “ideal MAP” during CPB, comparing the historically accepted “standard MAP” (50–60 mmHg) with the “high MAP” (70–80 mmHg) and with the “patient-tailored MAP”.

To investigate the risk of hypoperfusion and to evaluate whether the MAP during CPB is adequate to avoid tissue hypoxia, the serum lactate value, as index of tissue anaerobiosis/hypoperfusion, will be collected at different timepoints [15–18]. To date, several studies have analysed the trend of lactates intraoperatively and postoperatively, and hyperlactatemia demonstrated to be a predictive factor of postoperative mortality and morbidity [19]. In particular, Demers et al. [20] described how a peak of lactates >4 mmol/l during CPB relates to postoperative mortality. Ranucci et al. [21] confirmed that hyperlactatemia >3 mmol/l during CPB relates to postoperative major complications. However, both studies did not give information about the precise value of lactates reached, neither about the entire trend of lactates released during CBP. Therefore, differently from previous studies, the primary endpoint of this trial will be the peak value (absolute value) of serum lactates (Lmax) measured during CPB.

### Objectives {7}

#### Primary objective

To assess the best CPB management strategy in order to obtain the patient’s “ideal MAP,” comparing the “standard MAP” (50–60 mmHg) versus the “high MAP” (70–80 mmHg) versus the “patient-tailored MAP” (comparable to the preoperative mean pressure of the single patient). The measurement of blood lactate leakage during CPB will be used as index of hypoxia. Then, we will be able to compare the three strategies of MAP in terms of tissue perfusion.

#### Secondary objectives

To assess the intraoperative outcomes, through the following perfusion parameters:Intraoperative cerebral perfusion (through monitoring of the NIRS values)Intraoperative pulmonary perfusion (through Pa/FiO_2_ ratio, paO_2_, paCO_2_ at blood gas analysis, and VO_2_R and DO_2_ at CDI® Blood Parameter Monitoring System 550)

To assess postoperative clinical outcomes, through the following parameters:Intraoperative and postoperative low cardiac output syndrome (according to the values of vasoactive inotropic score, VIS) [22]Postoperative cardiac function (measuring left ventricular ejection fraction, LVEF)Postoperative respiratory failure (through the values of Lung Injury Score, LIS, scale) [23]Postoperative stroke and entity of transitory or permanent neurological damage (through score of modified Rankin Scale—mRS) [24]Postoperative acute kidney injury (through AKI score)Postoperative hepatic failure (measuring the hepatic function and coagulation indices)Postoperative gastrointestinal ischaemiaPostoperative cardiovascular death, or death due to other causes

To assess clinical outcomes at 30 days from surgery:Stroke and entity of the transitory or permanent neurologic damage (mRS score)Acute kidney injury (AKI score)Cardiac function (LVEF)Re-hospitalizationDeath for cardiovascular or other causes

#### Trial design {8}

The present study is an exploratory randomized controlled three parallel-group trial. The patient allocation is 1:1:1. The outcome of patients undergoing cardiac surgery and treated with a MAP standard during CPB is compared to patients treated with high MAP and patient-tailored MAP during CPB.

## Methods: participants, interventions and outcomes

### Study setting {9}

Coordinator Centre: Division of Cardiac Surgery, Azienda Ospedaliera Universitaria Integrata Verona, Italy.

Participating Centres:

Centre 1: Division of Cardiac Surgery at Ospedale Maggiore, Parma, Italy

Centre 2: Division of Cardiac Surgery at Azienda Sanitaria Universitaria Friuli Centrale, Udine, Itay

Centre 3: Division of Cardiac Surgery at Hospital Clinic de Barcelona, Barcelona, Spain

The study population includes all patients undergoing elective cardiac surgery. Enrolment and subsequent data collection will be performed in each participating centre. Statistical analyses will be performed by the Clinic Research Unit, University Hospital of Verona, Italy.

### Eligibility criteria {10}

#### Inclusion criteria

Age > 18 years and < 80 yearsElective surgeryIndex of surgical risk EuroSCORE II < 9%The following procedures will be considered: Isolated or combined with aortic or mitral valve surgery coronary artery bypass graft surgery for acute or chronic coronary artery disease isolated aortic valve replacement for aortic stenosis and/or aortic regurgitation; isolated mitral valve repair or replacement for mitral stenosis and/or mitral regurgitation; isolated ascending aorta surgery with or without aortic valve replacementSurgical approach through complete and/or mini sternotomyPreserved or mildly reduced left ventricular ejection fraction (LVEF ≥ 40%) at preoperative echocardiography.Patients with an estimated glomerular filtration rate (eGFR) ≥ 40 ml/min/mq calculated using the Modification of Diet in Renal Disease formula (MDRD)Signed informed consent

#### Exclusion criteria

Age < 18 years and >80 yearsReoperationEmergent, urgent and salvage proceduresEuroSCORE II > 9%Right thoracotomy approachesAny surgical procedure not listed above (i.e. tricuspid valve surgery, aortic root surgery, congenital heart diseases, surgery necessitating hypothermic circulation arrest, surgical ablation of atrial fibrillation, etc.)More than mild left ventricular dysfunction at preoperative echocardiogram (LVEF < 40%)Patients with critical preoperative state: any ventricular fibrillation or ventricular tachycardia, preoperative cardiac massage, preoperative ventilation before anaesthetic room, preoperative inotropes or mechanical circulatory support planned before cardiac intervention (i.e. during coronary angiography) and other conditions according to EuroSCORE II definition.Patients with an estimated eGFR < 40 ml/min/mq calculated using the MDRD or patients on dialysis.Patients with chronic obstructive pulmonary disease > 3 stage according to Global Initiative for Chronic Obstructive Lung Disease (GOLD) 2019 classification.Patients with severe preoperative hepatic failure (CHILD-PUGH ≥ B)Patient with severe symptomatic carotid atheromasia

### Who will take informed consent? {26a}

Participants will be asked by the research team to provide informed consent for study participation.

### Additional consent provisions for collection and use of participant data and biological specimens {26b}

No biological specimen will be preserved for future analysis.

## Interventions

### Explanation for the choice of comparators {6b}

“MAP standard” is the control group because the value of 50–60 mmHg has been historically considered the MAP “standard of care” during CPB at the Division of Cardiac Surgeries of all Participating Centres.

### Intervention description {11a}

The patients enrolled to elective cardiac surgeries will be evaluated during a pre-operative outpatient visit and widely informed about the chance to participate in the study. When patients undergo to the elective surgery general anaesthesia is administered and CPB is installed. The nominal flow for each patient will be 2.4 l/min/m^2^.

A continuous monitoring of blood pressure will be performed invasively by cannulating the radial or femoral artery, as is customary in cardiac surgery.

To keep the MAP values around those corresponding to the randomized group, vasodilator (if MAP overcomes the assigned MAP value) or vasoconstrictor drugs will be used (if MAP value is lower than the assigned group). The following drugs will be used: nitroglycerine at incremental dose of 0.01 mcg/kg/min for a vasodilator effect and norepinephrine at incremental dose of 0.01 mcg/kg/min for a vasoconstrictor effect. The treatment groups will be:

*Group 1: Standard MAP*: MAP values between 50 and 60 mmHg as control group.

*Group 2: High MAP*: MAP values between 70 and 80 mmHg.

*Group 3: Patient-tailored MAP*: MAP comparable to the patient’s pre-operative MAP. This one will be calculated by performing 3 blood pressure measurement in three different moments of the day before surgery (at 8 am, at 3 pm and at 9 pm), and will be calculated using the standard formula “Diastolic AP + 0.33 × (systolic AP − Diastolic AP)”. The preoperative MAP value obtained will be target during CPB, within a range of ± 10 mmHg.

## Procedures

### Preoperative

- Preoperative outpatient visit (7 days before surgery)Clinical evaluation of the patient and eligibility for the study through collection of anamnestic data and physical examination.

- Day before surgery:Collection of informed consent for participating the studyRandomizationMeasurement of preoperative MAP in every patient enrolled, regardless of the assignment group through randomization.Blood samples to assess: haemoglobin (Hb), haematocrit (Ht), white blood cells (WBC), platelets (Plt), C reactive protein (CRP), lactate dehydrogenase (LDH), prothrombin time (PT/INR), activated partial thromboplastin time (aPTT), fibrinogen and creatinine (mg/dl), lipase, pancreatic amylase, alanine aminotransferase (ALT), aspartate aminotransferase (AST), total bilirubin (Bil Tot), conjugated bilirubin (direct Bil), unconjugated bilirubin (indirect Bil), gamma-glutamyltransferase (GGT), alkaline phosphatase (ALP) and albuminArterial blood gas test (ABG) to evaluate preoperative lactatemiaCalculation of eGFR (according to MDRD) to evaluate preoperative renal functionEvaluation of preoperative mRS in case of stroke in amnestic history.

- Intraoperative (postoperative day, POD, 0)A continuous monitoring of blood pressure will be performed invasively by cannulating the radial or femoral artery, as is customary in cardiac surgery. Data of MAP will be recorded at the beginning of CPB, every 20 min until minute 300 and at the end of CPB.ABG after orotracheal intubation, at the beginning of CPB, every 20 min during CPB (eventually until minute 300), at the end of CPB, at the end of surgery. Data collected: lactates as organ perfusion index, Hb and Hct.Real-time and continuous monitoring of respiratory gases during CPB suggestive of the perfusion trend, through CDI ® 550 Blood parameter monitoring system (Terumo Europe) [25], data collection related to oxygen delivery (DO_2_), oxygen consumption (VO_2_) and oxygen extraction (O_2_ER), at the beginning of CPB, every 20 min (until minute 300) and at the end of CPB.Intraoperative monitoring of Near-Infrared Spectroscopy NIRS [26] defined as non-invasive measurement of cerebral microcirculatory blood flow. Data will be collected at anaesthesia induction, before skin incision, at the beginning of CPB, every 20 min (until minute 300), at the end of CPB and at the end of surgery.Monitoring of CPB and aortic cross-clamp timesCalculation of “vasoactive inotropic score” (VIS) [22] which relates the entity of inotropic and or vasoactive support. VIS max is obtained through the following calculation: [Dopamine dose (mcgkg/min)+ Dobutamine dose (mcg/kg/min) + 100 × Epinephrine dose (mcg/kg/min) + 50 × Levosimendan dose (mcg/kg/min) + 10 × Milrinone dose (mcg/kg/min) + 10,000 × Vasopressin dose (units/kg/min) + 100 × Norepinephrine dose (mcg/kg/min)]. The VIS will be calculated according to the length of surgery.Monitoring of nitroglycerine dose during surgery

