### Concealment mechanism {16b}

Use of a validated password website will ensure concealment.

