### Implementation {16c}

After a first researcher takes the informed consent forms, a second researcher will use the list of randomization to allocate the patient to one of the study arms. The study group will be revealed at the same time to the patient, the researchers, the first operator and the operating room staff.

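### Nothing requires the three readings that set the patient-tailored MAP target to be complete before the arm is disclosed, so some can be taken with the arm known

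*Protocol article*

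**What the plan says.** The preoperative part of the Procedures section gives the tasks in this order: "Day before surgery:Collection of informed consent for participating the studyRandomizationMeasurement of preoperative MAP in every patient enrolled". The measurement applies to all arms, and its wording refers to an assignment: it is the measurement "of preoperative MAP in every patient enrolled, regardless of the assignment group through randomization".

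Intervention description {11a} takes the blood pressure "in three different moments of the day before surgery (at 8 am, at 3 pm and at 9 pm". For Group 3 it then fixes the use of the result: "The preoperative MAP value obtained will be target during CPB, within a range of ± 10 mmHg".

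Implementation {16c} says that after consent "a second researcher will use the list of randomization to allocate the patient to one of the study arms", and that "The study group will be revealed at the same time to the patient, the researchers, the first operator and the operating room staff". Who will be blinded {17a} names only the researcher at the time of consent and the data analyst.

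On concealment, Sequence generation {16a} keeps the details of the blocking from those who enrol or assign, and Concealment mechanism {16b} states: "Use of a validated password website will ensure concealment".

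**The concern.** In most trials a baseline reading taken after allocation is a blemish on one descriptive variable. Here the preoperative MAP of a Group 3 patient is the target to which that patient is then managed. A cuff pressure also leaves room for judgement: a reading can be repeated, or one of several chosen. If the person taking it knows that the patient is in the tailored arm, that knowledge can enter the definition of the treatment. In Groups 1 and 2 the same reading sets nothing, so any influence would fall on one arm only.

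At stake is whether the tailored strategy under test really is the patient's own preoperative pressure, obtained in the same way as in the other arms.

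**Working it through.** No figure in the plan is at issue, and the sample size does not depend on this point. The check is one of timing.

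**Inputs**
- Day of randomisation: the day before surgery, listed after consent and before the MAP measurement (Procedures, Preoperative).
- Reading times: 8 am, 3 pm and 9 pm on that day (Intervention description {11a}).
- Disclosure: simultaneous to patient, researchers, surgeon and theatre staff, with no day or hour given (Implementation {16c}).
- Blinding of whoever takes the readings: none stated (Who will be blinded {17a}).

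**Readings taken with the arm known, by the time at which it becomes known**

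| Arm known | Readings before | Readings after |
|---|---|---|
| before 8 am | 0 | 3 |
| between 8 am and 3 pm | 1 | 2 |
| between 3 pm and 9 pm | 2 | 1 |
| after 9 pm, or on the morning of surgery | 3 | 0 |

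Only the last row keeps all the readings that define the target free of knowledge of the arm. No section requires that row. If the preoperative list is read as a sequence, the first row applies. If it is read as an unordered set of tasks for that day, any row is possible.

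**How far a target could move (illustration only)**

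The protocol does not say how the three readings are combined. Assume a simple average, and assume that one reading is off by e. The target then moves by e/3:
- e = 10 mmHg: 10/3 = 3.3 mmHg
- e = 15 mmHg: 15/3 = 5 mmHg

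Both the averaging and the size of e are assumptions, and neither comes from the document. The yardstick that fits is the ±10 mmHg tolerance around the Group 3 target, and both shifts lie inside it. The 10 mmHg between the top of the standard range (60) and the bottom of the high range (70) is not a fair comparison, because neither of those ranges depends on the readings.

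**List and website**

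Implementation {16c} has a researcher use the list, Concealment mechanism {16b} relies on a password website, and Sequence generation {16a} withholds the block details from those who assign. These agree if the list is reached only through the website, one allocation at a time. They conflict if the researcher holds the whole list for the centre. The text does not say which applies.

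**The case against.** The strongest reply is that the protocol never says the arm is known before the readings are complete. Simultaneous disclosure is not immediate disclosure, and no day or hour is given. The preoperative items may simply be that day's tasks. The statement that MAP is measured whatever the assignment can be read as a safeguard of uniformity, and fixed clock times with a fixed formula leave less room for selecting readings. All of this stands. It rules out saying that the target is measured unblinded. It does not answer the point that the plan permits it.

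A reader might go further in four ways that the document does not support:
- **An exposed list.** One might infer that a site researcher can see the next allocation. The website, the withheld block details and the separation of the consenting from the allocating researcher all speak against assuming this. Handling of the list is also a different matter from unblinded readings, since it bears on concealment before assignment.
- **Biased baseline lactate.** Preoperative lactate is a blood gas result with little room for observer influence. The planned primary comparison is a Mann-Whitney test of Lmax, and no baseline covariate is named for it.
- **Losses from cancelled operations.** No cancellation rate is given, and a 10% drop-out allowance is already made.
- **A motive to choose an easier target.** The Discussion reports difficulty in holding the assigned pressure, but its examples come from the high and standard arms, not the tailored arm.

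It can also be said that recruitment began on 02/05/2021, so a change now gives earlier and later patients different procedures. That is a genuine cost, but a small one, because what is measured stays the same and only the order changes.

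**Conclusion.** The point holds as a gap in the sequence of steps. Randomisation falls on the day before surgery, the readings that define the Group 3 target run until 9 pm that day, the arm is disclosed openly, and nobody taking the readings is said to be blinded. Unless allocation or disclosure happens to fall after 9 pm, one to three of the three readings can be taken with the arm known.

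The conclusion rests on the stated reading times, the stated day of randomisation and the absence of any rule that the readings come first. It does not rest on reading the list as a strict order, although that order and the wording point the same way. The effect on Lmax cannot be quantified from the document. The illustrative shift in the target is modest and depends on two assumptions. This is a cheap improvement worth making, not evidence that the tailored arm is biased.

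**What to change.** Amend the preoperative part of the Procedures section and Implementation {16c} so that, for every patient in every arm, the three readings are recorded and locked in the database before the allocation is issued. If that is impractical, they should be locked at least before the allocation is disclosed. Either way, disclosure comes after the 9 pm reading or on the morning of surgery. Holding back disclosure alone is enough to protect the readings and avoids the need to randomise late in the evening.

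This needs no new measurement and leaves the MAP ranges, the endpoint and the sample size unchanged. The operating team learns the arm later, and the procedure changes partway through a recruitment planned to run to 31/12/2026. The date of the change should be recorded so that patients enrolled before and after it can be told apart.

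Separately, and as a minor point, add one sentence that reconciles Sequence generation {16a}, Concealment mechanism {16b} and Implementation {16c}, stating that the website releases allocations one at a time.
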